## Abstract

•We report the protocol of a feasibility trial for a school-based sex education intervention.•The intervention challenges the gender-bias in sex education by especially targeting boys.•The interactive online intervention prompts adolescents to think about teenage pregnancy.•The cluster randomised controlled trial includes a process evaluation and health economics analysis.•This trial will test the feasibility of a larger trial to test for intervention effectiveness.

We report the protocol of a feasibility trial for a school-based sex education intervention.

The intervention challenges the gender-bias in sex education by especially targeting boys.

The interactive online intervention prompts adolescents to think about teenage pregnancy.

The cluster randomised controlled trial includes a process evaluation and health economics analysis.

This trial will test the feasibility of a larger trial to test for intervention effectiveness.

## Introduction

1

Teenage pregnancy remains a world-wide public health concern with rates in the US and UK among the highest in high-income countries (Finer and Zolna, 2011, Lawlor and Shaw, 2004). While teenage pregnancies have been gradually decreasing over the past decade, recent figures suggest pregnancy rates as high as 54.6 per 1000 women under 20 in the UK (ONS, 2012) and 67.8 per 1000 in the US (Kost & Henshaw, 2012). As many as half of these pregnancies end in legal abortion, reflecting the potentially unintended or unwanted nature of these conceptions (Kost and Henshaw, 2012, ONS, 2012). Although the life course for teenaged parents is not universally negative (Bonell, 2004, Duncan et al., 2010), the social disadvantage and exclusion that are linked to *unintended* teenage pregnancy are considered problematic (Harden, Brunton, Fletcher, & Oakley, 2009). Unintended adolescent pregnancy can lead to considerable adverse health problems for teenagers and their infants as well as generating emotional, social and economic costs for adolescents, their families and society (Beers & Hollo, 2009).

While unintended teenage pregnancy is a complex phenomenon that cannot be prevented through Relationship and Sexuality Education (RSE) alone (DiCenso et al., 2002, Elliott et al., 2013, Fullerton, 2004, Henderson et al., 2007, Shepherd et al., 2010, Silva, 2002, Stephenson et al., 2003, Wight et al., 2002), it is recognised that high quality RSE provides teenagers with a solid knowledge base on which to make informed decisions about their sexual behaviour, as well as being a vital aspect of improving holistic sexual health and wellbeing (Downing et al., 2006, Ellis and Grey, 2004, Ingham and Hirst, 2010, Oringanje et al., 2009, Swann et al., 2003). Reflecting the importance of RSE in the UK, the governments of Northern Ireland (NI), England and Scotland all emphasise the need to achieve a reduction of teenage pregnancy rates via the implementation of RSE in schools and see this as a key objective in their sexual health policies (Department of Health, 2013, DHSSPS, 2008, The Scottish Government, 2011).

In recent times, there has been recognition that teenage men have a vital yet neglected role in reducing teenage pregnancies (Alan Guttmacher Institute, 2002, Lindberg and Kost, 2014, Marsiglio, 2006, Saewyc, 2012, Smith et al., 2005, Swann et al., 2003). When young men do receive RSE concerning pregnancy it is often via programmes and interventions that are directed towards girls and which ignore the fact that males and females are affected differently by gender norms and values relating to pregnancy (World Health Organisation, 2011). Thus, internationally, researchers and policy makers have called for targeted and scientifically evaluated RSE interventions which meet the sexual health needs of young men (Juszczak and Ammerman, 2011, Saewyc, 2012, World Health Organisation, 2011).

While some behavioural programmes targeting adolescent sexual risk-taking behaviour have demonstrated only modest success (DiCenso et al., 2002, Shepherd et al., 2010), systematic reviews have identified the characteristics of effective RSE programmes which might help optimise their potential impact on sexual risk-taking behaviours (Bailey et al., 2010, Guse et al., 2012, Kirby et al., 2006, Kirby, 2007, Kirby, 2002, Noar et al., 2010, Robin et al., 2004, Shepherd et al., 2010). These include the use of theoretically-based interventions targeting sexual and psychosocial mediating variables such as knowledge, attitudes, self-efficacy, intentions, perceptions of risk, and perceptions of peer norms which are theoretically linked to sexual behaviour change (Ajzen and Madden, 1986, Cane et al., 2012, Michie et al., 2013, Rivis et al., 2009); the use of culturally-sensitive and gender-specific interventions (Marsiglio, 2006, Ries and Sonenstein, 2006); the use of interactive modalities which promote personal identification with the educational issues and engagement of young people (Bailey et al., 2010, Guse et al., 2012); the use of skills-building components (Oringanje et al., 2009, Wight et al., 1998); the involvement of parents in the RSE process (Grossman, Frye, Charmaraman, & Erkut, 2013); and the facilitation of linkages with sexual health support services (Coyle et al., 1999).

The *If I Were Jack* intervention represents an innovative combination of these different components and is therefore predicted to decrease young people's sexual risk-taking behaviour in relation to avoiding teenage pregnancy. The aim of the study described in this protocol is to explore the feasibility of determining, in a cluster randomised trial, whether this combination of components can effectively increase boys’ and girls’ intentions to avoid an unintended teenage pregnancy.

## Methodology

2

### Background to the study

2.1

The study is a cluster randomised feasibility trial with embedded process and cost-effectiveness evaluations. The project began in May 2014 and will run for two years (see project flowchart, Fig. 1). Following the UK Medical Research Council's *Guidelines for the Development and Evaluation of Complex Interventions* (Medical Research Council, 2008), the current phase of research was preceded by focused programme development (Aventin, Lohan, O’Halloran, & Henderson, 2014) which involved identification of the relevant evidence base, development of a theoretical understanding of the phenomenon of unintended teenage pregnancy in relation to young men, and exploratory mixed methods research examining the acceptability of the *If I Were Jack* interactive film among young men, teachers and RSE specialists (Lohan et al., 2011, Lohan et al., 2012).

**Fig. 1 fig0005:**
[figure not shown]
Jack Feasibility Trial Project Flowchart.

### Intervention

2.2

Informed by research on adolescent men's attitudes towards unintended pregnancy and the best available evidence on the components of effective RSE interventions, the intervention was designed to fit within the NI RSE curriculum by a team of researchers at Queen's University Belfast working with experts from the Department of Health, Social Services and Public Safety NI, the Public Health Agency NI, and the Council for the Curriculum, Examinations and Assessment in NI, as well as RSE specialists, teachers, parents and young people. Although produced in NI, the intervention will have strong cultural resonance for Ireland and the UK as a whole and could be adapted for use internationally.

This 4-week programme is composed of a number of elements (Table 1):i.*If I Were Jack* interactive video drama (IVD) which tells the fictional story of 16-year old Jack who has just found out that his girlfriend is pregnant. Seated at individual computers, pupils are immersed in Jack's story and are asked to consider how they would feel and what they would do if they were Jack;ii.Classroom materials for teachers containing four detailed lesson plans with specific classroom-based and homework activities which include group discussions, role-plays, worksheets, and a parent-pupil exercise;iii.60-min training session delivered by a researcher to teachers wishing to implement the intervention detailing the components of the intervention and its delivery and highlighting the research procedures;iv.60-min information and discussion session for parents/guardians delivered by RSE teachers during the first week of the implementation period (prior to the parent/guardian homework activity; andv.Detailed information brochures, factsheets and a dedicated website (www.qub.ac.uk/IfIWereJack) about the intervention and unintended teenage pregnancy in general for schools, teachers, teacher trainers, young people and parents.

**Table 1 tbl0005:** Psychosocial and behavioural components of the *If I Were Jack* intervention.

Component	Aim	Measurement
Knowledge	Increase knowledge about: ways of avoiding unintended pregnancy; roles and responsibilities of young men in relation to unintended pregnancy; possible negative relational, social, emotional and financial consequences of unintended pregnancy; and sources of information and support for unintended pregnancy	Individual assessment. Total score on 10 knowledge items. Selected items from the Mathtech Knowledge Inventory (Kirby, 1984); and SKATA (Fullard et al., 2005)

Communication skills	Increase skills communicating with parents and peers about avoiding unintended pregnancy	Comfort Communicating about Avoiding Unintended Teenage Pregnancy Scale(parents, peers and professionals) using adapted items from the Mathtech Behaviour Inventory (Kirby, 1984)

Attitudes about unintended pregnancy	Increase anticipated regret about the consequences of unintended pregnancy on current life and future goals	Items from the newly developed Intention to Avoid Unintended Teenage Pregnancy Scale

Social influences	Increase awareness of peer norms, stereotypical gender norms and parental attitudes and beliefs about teenage pregnancy *Gender norms:* increase perception that both men and women have roles and responsibilities in avoiding and dealing with the consequences of unintended pregnancy *Peer norms:* increase perception that most peers are not sexually active and use contraception when they are *Parental values & beliefs:* increase awareness of parental attitudes and beliefs about unintended pregnancy	*Male Role Gender norms:* Male Role Attitudes Scale (Pleck et al., 1993) and knowledge items relating to responsibility for avoiding pregnancy. *Peer norms:* Knowledge items about sexual behaviour/contraceptive use among peers and sexual socialisation instrument (peer sub-scale) (Lottes & Kuriloff, 1994) *Parental values & beliefs:* Sexual socialisation instrument (parent sub-scale) (Lottes & Kuriloff, 1994)

Beliefs about capabilities	Increase perceived behavioural control to avoid unintended pregnancy (say no to sex or obtain and use contraception correctly) and increase self-efficacy to communicate about avoiding unintended pregnancy with parents, peers & professionals	Sexual self-efficacy scale using an adapted version of the Sexual Self-Efficacy Scale (Rosenthal, Moore, & Flynn, 1991)

Intentions	Increase strength of intention to avoid unplanned teenage pregnancy	Intentions to avoid unintended teenage pregnancy scale (constructed by research team)

Sexual behaviour	Abstinence from sexual intercourse (delay initiation of sex or return to abstinence) or avoidance of unprotected sexual intercourse (consistent correct use of contraception)	Sexual behaviour items (ever had sexual intercourse; frequency of sexual intercourse; contraception use ever/at last intercourse). Items adapted from previous sexual health surveys (Carswell et al., 2012, Elliott et al., 2010).

Pregnancy	Avoidance of unintended pregnancy	Ever pregnant

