### Outcome measures and assessment instruments

2.4

Key outcomes are the quality of intervention implementation and recruitment and retention of participants. The study will also pilot the feasibility and acceptability to participants of providing demographic data and answering sexual behaviour questions measuring the proposed primary and secondary outcomes for a future, larger phase III trial. Drawing upon the United Kingdom Medical Research Council Guidelines (MRC, 2008), a phase III study is a randomised controlled trial in which the sample size is statistically powered to capture the effectiveness of an intervention.

In a phase III trial, a reduction in unintended adolescent pregnancy rates would be the ideal primary outcome measure. However, the sample size would need to be large in order to detect an important change in this. We will therefore use surrogate measures associated with reductions in unintended pregnancy: abstinence from sex or avoidance of unprotected sex (2 years past baseline). In the feasibility trial, we will pilot the feasibility and acceptability of collecting these data from pupils at five and nine-month follow-up.

Secondary outcomes in a phase III trial would be six-month impacts on knowledge, attitudes, skills and intentions relating to avoiding teenage pregnancy. These short-term impacts are hypothesised to lead to increased intention to avoid teenage pregnancy. In this feasibility trial, we will collect data from pupils using items developed specifically for use in the study as well as items from a number of adapted standardised measures to provide broad estimates of effect sizes and the feasibility and acceptability of the questions. The measures were chosen because the constructs they measure map closely to the theoretical framework underpinning the intervention. As part of the study, we will develop a measure of intentions to avoid unplanned pregnancy. We will investigate the association between intentions at baseline and behaviour (abstinence or avoidance of unprotected sex) at follow-up. While regression analyses would be used in the main trial to model the impact of intentions on behaviour, the feasibility study is not powered to detect statistical differences and we will present descriptive statistics relating to the primary outcomes.

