**Knowledge** will be measured with items which replicate or have been adapted from similar items in existing validated sexual knowledge scales [Sexual Knowledge & Attitudes Test for Adolescents (Fullard, Johnston, & Lief, 2005); Mathtech Knowledge Inventory (Kirby, 1984)] and questionnaires used in previous sexual health studies with adolescents (Carswell et al., 2012, Elliott et al., 2010).

**Communication skills** will be assessed using adapted versions of the comfort in communicating with peers and parents about sex and birth control sub-scales of the Mathtech Behaviour Inventory (Kirby, 1984). We have adapted the sex sub-scale so that it refers to comfort communicating about avoiding pregnancy and added a new item which assesses comfort in communicating with professionals about unintended pregnancy and contraception.

**Attitudes towards unintended pregnancy** will be measured using items from a newly developed measure of intention to avoid unintended pregnancy (see below).

**Awareness of stereotypical gender norms** will be assessed using the Male Role Attitudes Scale (Pleck, Sonenstein, & Ku, 1993) and attitude items relating to male/female responsibility for avoiding unintended pregnancy.

**Awareness of peer norms and parental values and beliefs** relating to avoiding unintended pregnancy will be assessed using the peer and parent sub-scales of the Sexual Socialisation Instrument (Lottes & Kuriloff, 1994).

**Beliefs about capabilities in avoiding unintended pregnancy** and communicating about avoiding unintended pregnancy will be measured using an adapted version of the Sexual Self-Efficacy Scale (Rosenthal, Moore, & Flynn, 1991).

A measure of **intention to avoid teenage pregnancy** will be developed as part of the study.

**Avoidance of sexual risk-taking behaviour** (abstinence from sexual intercourse or avoidance of unprotected sex) will be assessed using eight items adapted from previous sexual health surveys (Carswell et al., 2012, Elliott et al., 2010). Incidence of pregnancy will be recorded in order to establish **pregnancy outcomes.**

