#### Feasibility trial

2.8.1

All pupils in Year 11 in the seven recruited schools will be invited to participate, with the schools in the intervention group receiving a four-week intervention, which replaces normal RSE practice, and the schools in the control group continuing with normal practice. Participating pupils will be in the study for approximately one year and asked to complete a questionnaire during an RSE lesson at baseline and at five and nine months after implementation. Schools will be encouraged to allow pupils to complete the questionnaire online but, if this is not feasible, will be permitted to use paper questionnaires. A fieldworker will be in attendance during data collection to administer the questionnaire or oversee access to the online survey. Questionnaires and envelopes (or links to the online survey) will be left for absent pupils to complete. Identical procedures will be adhered to at each of the two follow-up surveys.

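### No behaviour or pregnancy item listed in Table 1 is tied to the period after baseline, and the stated analysis does not use baseline behaviour

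*Protocol article*

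**What the plan says.** Table 1 in section 2.2 sets the behavioural aim as abstinence ("delay initiation of sex or return to abstinence") or avoiding unprotected sex through consistent, correct contraception. The measures beside that aim are "ever had sexual intercourse; frequency of sexual intercourse; contraception use ever/at last intercourse". The pregnancy row has one measure, "Ever pregnant".

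Section 2.4 says that risk-taking behaviour "will be assessed using eight items adapted from previous sexual health surveys", and that "Incidence of pregnancy will be recorded". It names abstinence or avoidance of unprotected sex as the intended phase III primary outcome. It also states: "We will investigate the association between intentions at baseline and behaviour (abstinence or avoidance of unprotected sex) at follow-up".

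Under section 2.8.1 the same pupils answer "at baseline and at five and nine months after implementation". Section 2.7 places randomisation after the baseline survey. Section 2.9 takes behavioural effect sizes from the difference in proportions between arms, and mentions neither new events nor baseline status. It also says that no inferential analysis will be done.

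**The concern.** The outcome concerns what pupils do after the programme, but the listed measures do not isolate that period. A lifetime item answered at five or nine months also counts events from before randomisation, which the intervention cannot have influenced. Two things are at stake.

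- **Effect sizes for phase III.** If baseline status is not used, a difference between arms that existed before randomisation reappears at follow-up and looks like an effect. Seven randomised schools give little protection against such a difference.
- **The intention-behaviour link.** Pupils who have already had sex may hold different intentions because of it. If the follow-up measure is still positive because of that earlier event, the association looks like prediction although the order of events is reversed.

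The trial also exists partly to pilot the phase III endpoint. Items that cannot express that endpoint for sexually experienced pupils would leave part of the piloting undone.

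**Working it through.** **1. The plan's own figure.** Section 2.6 expects about 630 pupils from seven schools, with a mean year size of 114 (median 113) and 80% consent. 7 × 114 × 0.8 = 638 and 7 × 113 × 0.8 = 633, so the figure reproduces and is not in dispute. The article gives no rate for sexual experience or onset, so every rate below is an assumption.

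**2. Items against aims.**

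| Item in Table 1 | What it covers | What it cannot show alone |
|---|---|---|
| Intercourse, ever | Lifetime | Return to abstinence |
| Contraception, ever | Lifetime; one protected act suffices | Consistent use |
| Contraception, last act | One act, possibly before baseline | Consistent use since baseline |
| Frequency of intercourse | No period stated | Depends on the unseen period |
| Pregnancy, ever | Lifetime | Incidence |

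**3. What linked baseline answers recover.** For an ever item:

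- No at baseline, then no: no event.
- No at baseline, then yes: first event in the interval.
- Yes at baseline, then yes: nothing is known about the interval.

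Linking therefore recovers first events. It does not recover return to abstinence or consistent use in pupils who were already active.

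**4. Is the effect diluted on the planned scale?** Let p0 be the share positive at baseline and i the new onset by nine months among the rest. Assume a true risk ratio of 0.70 on onset.

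- Control, ever item: p0 + (1 − p0)i
- Intervention, ever item: p0 + (1 − p0)(0.7i)
- Difference: 0.3(1 − p0)i

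Counting only new events over all pupils also gives 0.3(1 − p0)i. With i = 10%:

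| p0 | Control | Intervention | Difference (points) | Control positives that pre-date baseline |
|---|---|---|---|---|
| 5% | 14.50% | 11.65% | 2.85 | 34% |
| 15% | 23.50% | 20.95% | 2.55 | 64% |
| 30% | 37.00% | 34.90% | 2.10 | 81% |

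The difference in proportions is not diluted. The 3.0 points obtained among baseline-negative pupils only (0.10 − 0.07) differs because the denominator differs.

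**5. Baseline imbalance with no intervention effect.** If p0 differs between arms by d and onset is equal, the follow-up difference on an ever item is d − d·i = d(1 − i).

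| d (points) | i = 5% | i = 10% | i = 20% |
|---|---|---|---|
| 5 | 4.75 | 4.5 | 4.0 |
| 10 | 9.5 | 9.0 | 8.0 |

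Among baseline-negative pupils the same scenario gives i − i = 0. At i = 10%, the spurious 4.5 to 9 points exceeds the 2.1 to 2.85 points that a true risk ratio of 0.70 would produce in step 4.

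**6. Intention and behaviour.** On an ever item, a pupil positive at baseline must be positive at follow-up. Any baseline association between intention and past sex is therefore carried into the follow-up association. At p0 = 15% and i = 10%, 64% of control-arm positives at follow-up would be pupils already positive when intention was first measured.

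**The case against.** The strongest reply is that Table 1 is shorthand. Section 2.4 refers to eight items whose full wording is not shown, and section 2.5 says that the questionnaire is still to be developed and piloted. Recall periods may be in it. The same pupils also answer at baseline, so first events can be derived from linked answers, and linkage is already needed for the intention-behaviour association. The key outcomes are implementation, recruitment and retention, and the behavioural analysis is descriptive.

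Much of this stands, and it rules out several stronger readings that a reader might infer:

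- **That every item is a lifetime item.** Frequency and contraception at last intercourse are not. With a suitable window, frequency could detect a return to abstinence.
- **That a true relative reduction is shrunk by the share of events before baseline.** That holds for a ratio: in step 4 the ever-item risk ratios would be 0.80, 0.89 and 0.94. Section 2.9 plans a difference in proportions, where no such dilution occurs.
- **That sexually experienced pupils are failures whatever happens.** The outcome is abstinence or avoidance of unprotected sex, and no section defines it as ever having had sex.
- **That boys cannot register a pregnancy.** This rests on a two-word label; the item as put to boys is not shown.
- **That the item set cannot measure the endpoint at all.** The unseen wording prevents that conclusion.

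The reply does not remove two gaps. Linked answers say nothing about the interval for pupils positive at both times, and an analysis plan cannot add a recall period to a question already asked. The analysis, as stated, also does not say that baseline behaviour is used.

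**Conclusion.** The point holds in limited form. As listed, no behaviour or pregnancy measure is confined to the time after baseline. The lifetime items cannot alone show the aims set for pupils already sexually active, and the two descriptions of pregnancy (lifetime and incidence) are different quantities. If lifetime items are compared as plain proportions, about 90% of any baseline imbalance passes into the effect estimate at 10% onset (95% at 5% onset, 80% at 20%). The intention-behaviour association is confounded by past behaviour.

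These sizes rest on assumed onset, assumed imbalance, and lifetime items being used directly in the follow-up comparison. No test is invalidated, because none is planned. What suffers is the rough effect sizes and the piloting of the phase III endpoint, both of which are stated purposes of this trial. It is worth correcting, at moderate priority.

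**What to change.** 1. At five and nine months, ask about sex, any sex without contraception, and having been pregnant or caused a pregnancy, each since baseline. A window fixed at baseline stays the same for pupils who miss the five-month survey.
2. Keep the ever items at baseline, and use one definition of the pregnancy measure in Table 1 and section 2.4.
3. Report behaviour outcomes by baseline sexual experience, or as new events among pupils negative at baseline.
4. Present the intention-behaviour association within strata of baseline behaviour.

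Restricting that association to control pupils, or relating five-month intention to behaviour between five and nine months, is optional.

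The cost is rewording a few of the eight items and somewhat less comparability with the surveys they come from. Items 3 and 4 use baseline answers already collected and need only linked responses.
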